## Background

The number of cancer survivors in Australia is increasing due to population ageing, growing incidence of some cancers and improvements in early detection and treatment [1]. However, cancer survivorship care is a neglected phase of the cancer care trajectory. The medical system tends to focus primarily on curing the cancer rather than managing the after-effects of treatment. Cancer and its treatments are often associated with adverse physical and psychological effects that can persist for months or years after treatment. Such after-effects can include fatigue, functional impairment, weight gain, sleeping difficulties and reduction in quality of life [2-7].

Increasing physical activity provides a non-pharmacologic strategy for the prevention and/or alleviation of many of these effects. Evidence has consistently indicated that physical activity has a positive impact on physiological outcomes (e.g. cardiovascular fitness, physical functioning, immune function, muscle strength, body composition, nausea and fatigue) and psychological wellbeing (e.g. mood, self-esteem, anxiety and depression) following a cancer diagnosis [8-13].

Despite these health benefits, many cancer survivors are not sufficiently physically active [14]. Cancer survivors living in rural and remote areas are at even higher risk of being physically inactive and experiencing negative effects after treatment than their urban counterparts [15,16]. This may be due to unique features of the rural environment including geographic diversity, social isolation, limited access to treatment services and facilities and the burden of travel distances [17]. Thus, there is a need for tailored, broadly accessible health promotion interventions to improve outcomes for survivors living in both metropolitan *and* rural areas.

The purpose of this paper is to describe the protocol of the STRIDE 12- week intervention, which has been specifically designed to test the effectiveness of an online resource for increasing regular walking and improving health and quality of life outcomes among cancer survivors living in metropolitan and rural areas. The trial also aims to identify whether there are region specific (metropolitan versus rural) predictors of successful engagement with the intervention. To our knowledge, it will be the first to use ratings of perceived exertion (RPE) and daily affect to deliver individualised, incremental step goals for participants relative to their baseline values.

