### Statistical considerations

#### *Sample size calculation*

A priori power calculations determined that a sample of 44 participants per group (n = 88) is needed to detect moderate effect sizes (r = 0.30-0.50) with 80% power and a significance level (alpha) of 0.05. Allowing for 20% dropout, 55 participants are required per group. Allowing for adjustment by baseline measure (r = 0.05) a total of 41 participants per group (n = 82) will be recruited.

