#### *Analytic plan*

Data will be entered and analysed using the IBM SPSS version 21 (SPSS, Inc, Chacago, IL) statistical software package. The intent-to-treat principle will be applied and the significance level will be set at 0.05. Baseline comparisons of demographic outcomes will be performed using independent samples t-tests. The primary outcome (number of steps/day) will be reported as independent samples t-tests comparing change scores in the two randomisation groups. Change scores for the secondary outcomes (health measures, diet quality and quality of life) will be calculated for each variable and compared between treatment and control groups using parametric or non-parametric procedures as appropriate for the data distributions.

Random effects mixed modelling will be used with time (0, 12, and 24 weeks) and group allocation (Intervention, Control) as the fixed factors. A time by group interaction term will be used to formally test the aims of the study.

Time by region (rural versus metropolitan) repeated measures ANOVA will be used to examine differences in the primary and secondary outcomes between groups over time. Sociodemographic factors and diet will be controlled for in the analysis.

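### The time-by-region repeated measures ANOVA by default keeps only participants seen at every visit, although the mixed model already planned for the arm comparison would keep partial records

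*Protocol article*

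**What the plan says.** All statements below are from the protocol article.

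- **Regional analysis (Analytic plan):** "Time by region (rural versus metropolitan) repeated measures ANOVA will be used to examine differences in the primary and secondary outcomes", comparing groups across time.
- **Arm comparison (Analytic plan, preceding paragraph):** "Random effects mixed modelling will be used with time (0, 12, and 24 weeks"), with allocation as the other fixed factor. The time-by-group term tests the study aims. Region is not in this model.
- **Principle (Analytic plan):** "The intent-to-treat principle will be applied", with no limit to particular analyses.
- **Software (Analytic plan):** "Data will be entered and analysed using the IBM SPSS version 21".
- **Dropout (Sample size calculation):** "Allowing for 20% dropout, 55 participants are required per group". The final target, after a baseline adjustment, is 41 per group, 82 in all.
- **Visits (Outcome measures):** baseline, end of programme (week 13, shown as 12 weeks in the mixed model) and 3-month follow-up (24 weeks). A pedometer week counts only with 10 hours of wear on four of seven days, one of them at a weekend.
- **Rural setting (Background):** possible reasons for rural inactivity and worse after-effects include "limited access to treatment services and facilities and the burden of travel distances".

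**The concern.** The same outcomes at the same visits would be analysed on two sets of people: partial records kept for the arm question, complete cases only for the regional one. Someone who attends week 13 but misses the final visit drops out of the regional analysis altogether, and an observed week-13 value is discarded. The plan gives no reason for the second method, and it sits poorly with a general intent-to-treat statement.

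Region matters to this trial. The Abstract and Background name metropolitan and rural survivors in the purpose, and the Discussion stresses rural reach. A regional contrast from completers is less precise than it need be. If the reasons for leaving differ by region, it may also be distorted.

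**Working it through.** **Who remains.** The plan's dropout step reproduces: 44 / (1 − 0.20) = 55 per group. Applying the same 20% to the 82 to be recruited:

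- 82 × 0.80 = 65.6, about 66 complete cases for any outcome.
- For steps, a visit without a valid pedometer week is also missing. If 95% of weeks are valid at each visit (assumed), 65.6 × 0.95³ = 56.2. If 90%, 65.6 × 0.90³ = 47.8.

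**Assumed inputs for precision and bias.** The document gives none of these: 25 of 82 rural (57 metropolitan); unit SD at each visit; correlation 0.7 between visits; no true regional difference; everyone seen at week 13; final visit missing for 15% metropolitan and 32% rural. Overall dropout is (57 × 0.15 + 25 × 0.32) / 82 = 16.55 / 82 = 20.2%, which matches the plan. The contrast is rural minus metropolitan change from baseline.

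**Week-13 precision, random dropout.** Variance of a change score = 2 × (1 − 0.7) = 0.6.

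- All observed: √[0.6 × (1/25 + 1/57)] = 0.186.
- Completers: 25 × 0.68 = 17 rural and 57 × 0.85 = 48.45 metropolitan; √[0.6 × (1/17 + 1/48.45)] = 0.218.
- Simulation of 2,000 trials gives 0.186 and 0.223. The second is slightly above the formula because completer numbers vary between trials. Ratio 0.223 / 0.186 = 1.20.

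**Week-24 precision, random dropout.** Simulated SE is 0.220 for completers against 0.212 to 0.215 for a likelihood fit to all visits. Ratios: 0.220 / 0.212 = 1.04 and 0.220 / 0.215 = 1.02. The gain is small because the missing week-24 values are only partly predicted by earlier visits.

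**Bias.** Rural dropout is now made to depend on poor week-13 change (log-odds per SD).

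| Dropout slope | Completers, week 13 | All observed, week 13 |
|---|---|---|
| 0 (random) | 0.005 | 0.010 |
| 0.5 | 0.123 | 0.000 |
| 1.0 | 0.229 | −0.001 |

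At week 24 the completer bias for slopes 0.5 to 1.0 is about 0.06 to 0.12 SD.

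**Which kinds of dropout matter.** A second simulation (3,000 trials; 41 per region; correlation 0.5; no true difference) gives the type I error of the completer time-by-region test at nominal 5%.

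| Dropout | Type I error |
|---|---|
| 20% in both regions, random | 5.8% |
| 30% rural, 10% metropolitan, random | 5.6% |
| Same outcome-related rule in both regions | 5.4% |
| About 30% rural, related to poor change; 10% metropolitan, random | 21.6% |

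Only the last row departs clearly from nominal. There the completer bias is 0.35 SD at week 12 and 0.17 SD at week 24. A likelihood fit to all visits reduces both to about 0.01 SD.

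**The case against.** Four stronger readings are tempting, and the document supports none of them.

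- **That the ANOVA breaks intent-to-treat.** The principle protects the randomised comparison. Region is not randomised, and the arm question has its own mixed model. The regional method is inconsistent with an unrestricted statement of the principle; that is all that can be said.
- **That 20% dropout produces a false regional difference.** It does not. Random dropout, even if unequal by region, costs precision only, and so in effect did the same outcome-related dropout in both regions. The document gives no dropout by region.
- **That rural participants will miss visits because of travel.** The Background offers travel burden as a possible reason for rural inactivity and worse after-effects, not for missed assessments. The Abstract places the trial partly in community health services, so visits may be local. Regional dropout is plausible but not established.
- **That missing data are left unhandled.** Imputation before the ANOVA is neither stated nor excluded, and an article may leave it to a fuller plan. Deletion is the software default, not a stated rule. Three visits in the ANOVA is likewise inferred from the wording on change over time and the visit schedule.

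Two limits on the size also stand. The simulated dropout all falls after week 13 and depends on observed data, which favours the mixed model. People who leave before week 13 contribute only a baseline value, from which little is recovered. Dropout driven by unobserved outcomes would bias either method.

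The core point survives. Even if imputation were intended, nothing explains why a second method, which needs it, is fixed beside a model that does not.

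**Conclusion.** The point holds as an avoidable weakness in a stated secondary analysis. By default about 66 of 82 participants would enter the regional ANOVA, and observed week-13 data would be discarded. The certain cost is precision: under the assumed split, correlation and dropout, an SE about 20% larger at week 13 but only 2-4% larger at week 24. Bias of about 0.12-0.23 SD at week 13 and 0.06-0.12 SD at week 24 is conditional on outcome-related dropout that differs by region, with assumed slopes of 0.5-1.0. The document neither shows nor excludes that pattern. The primary, randomised comparison does not depend on this analysis.

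**What to change.** Replace the repeated measures ANOVA with the linear mixed model already planned, extended to time, group, region and their interactions. Treat time as a factor, use an unstructured covariance over the three visits, and include every observed visit. State which regional term is the test: time by region asks whether change differs by region, while time by group by region asks whether the intervention effect does. The present sentence leaves this unclear.

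The cost is a few lines of wording and trivial extra analysis, with the same software, data and visits. The model still assumes that data are missing at random, and it recovers little from those who leave before week 13.

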## Discussion

Cancer survivors commonly experience negative effects following cancer and its treatment(s), including fatigue, functional impairment, weight gain and cancer recurrence [2-6]. Engagement in regular physical activity may ameliorate or prevent such adverse effects and enhance quality of life [8-13]. This research involves the development and trial of an online resource to assist cancer survivors in both metropolitan and rural areas to become more physically active and to adopt a healthier diet. Currently, there are no existing step guidelines for cancer survivors. A value of 10,000 steps per day for healthy adults is often reported in the media as an appropriate goal. However, such a universal goal may not be achievable for those who have had cancer. The STRIDE study will contribute significantly to the literature as it will use RPE and daily affect to create individualised, incremental step goals relative to the individual’s baseline values. Thus the intervention will be tailored to the survivor’s current capacity for physical activity. The online delivery of the program will allow wide community reach and dissemination, which is particularly important among cancer survivors in rural communities who have reduced access to services and facilities compared to their urban counterparts. Specifically, the results from this study could form the basis of the development of a specific exercise prescription for this population.

## Abbreviations

STRIDE: Steps toward improving diet and exercise; RPE: Rating of perceived exertion.
